**4.b University of Washington Primary Infection Clinic (PIC)**

Since 1992, *319* subjects with HIV-1 infection have been enrolled and followed for a median of *42 (range 0-184)* months in an observational cohort at the PIC. **Table 2** shows the demographic characteristics of subjects with primary HIV-1 infection enrolled in the PIC cohort compared to persons with predominantly established HIV-1 infection reported to Public Health - Seattle & King County [181]**.** *Seventy-eight subjects* were enrolled within 30 days of their estimated dates of HIV-1 infection. *Women and African/African-American subjects are under-represented relative to the number of individuals diagnosed with HIV-1 infection in King County because the majority of individuals comprising these categories are African immigrants who did not acquire their infection locally. Additional details regarding the inclusion of women and minorities are provided in* ***8. Protection of Human Subjects.***

ARV treatment was started in some subjects through non-randomized research protocols or through primary care providers. Despite the existence of national guidelines that have recommended the consideration of therapy during acute HIV-1 infection, the proportion of PIC subjects starting therapy immediately following HIV-1 acquisition has decreased over time, likely due to an increasing number of studies that have found no direct evidence of sustained clinical benefits in subjects treated during primary HIV-1 infection*. Forty-eight (67%) of 72 subjects enrolled in 1999-2001, 40 (68%) of 59 subjects enrolled in 2002-2004, and only 22 (39%) of 57 subjects enrolled in 2005-mid 2008 chose to receive ARV therapy in the first year after HIV-1 acquisition.* Plasma and PBMCs are stored and available for each of these subjects throughout study follow-up, and records of CD4+ T-cell counts, HIV-1 RNA levels, and clinical endpoints are available at regular intervals.

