**4.g Transmitted HIV-1 drug resistance among subjects enrolled in the PIC Cohort study**

A New Investigator Award from the UW Center for AIDS and STD to [name] provided supplemental funding to SeaPIP for a pilot project to evaluate the prevalence and impact of transmitted low-frequency HIV-1 drug resistance in subjects with primary HIV-1 infection. Consensus sequencing and OLA were performed on the first available plasma and PBMC specimens from ARV-naïve subjects enrolled in the UW PIC cohort between 1996 and 2005. Subjects were preferentially selected for study if they had enrolled in the cohort within 30 days of HIV-1 infection or if they initiated ARV therapy during follow-up. Demographic and other characteristics of subjects were otherwise similar to the entire PIC cohort.

*Baseline resistance test results are available from 100 subjects tested to date. Consensus sequencing and OLA were performed using stored frozen plasma and PBMCs obtained a median of 29 (IQR 19-66) and 30 (IQR 19-66) days after HIV-1 infection, respectively. Consensus sequencing detected transmitted HIV-1 drug resistance in 6 (6%) of 100 subjects, and OLA detected low-frequency mutations in 28 (30%) of the 94 subjects who had no mutations detected by consensus sequencing. OLA identified significantly more subjects with transmitted resistance in both plasma and PBMCs compared to consensus sequencing (****Table 4****).*

**Table 4: Number of ARV-naïve subjects with transmitted** HIV-1 drug resistance at baseline

| **4a:** OLA v consensus sequencing in plasma | | | |
| --- | --- | --- | --- |
|  | | OLA | |
| - | + |
| sequencing | - | 74 | **21** |
| + | **0** | 5 |

| **4b**: OLA v consensus sequencing in PBMCs | | | |
| --- | --- | --- | --- |
|  | | OLA | |
| - | + |
| sequencing | - | 78 | **16** |
| + | **2** | 4 |

| **4c**: consensus sequencing in plasma v PBMCs | | | |
| --- | --- | --- | --- |
|  | | PBMCs | |
| - | + |
| plasma | - | 94 | **1** |
| + | **0** | 5 |

| **4d:** OLA in plasma v PBMCs | | | |
| --- | --- | --- | --- |
|  | | PBMCs | |
| - | + |
| plasma | - | 66 | **8** |
| + | **14** | 12 |

+ = subjects w/ ≥1 mutation or mixture.

- = subjects w/o mutations or w/ indeterminate results

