**5. Research Design and Methods**

**5.a Overview of study design and rationale**

The studies proposed in this section will provide a better understanding of the prevalence and dynamics of low-frequency HIV-1 drug resistance mutations in ARV-naïve subjects during primary HIV-1 infection (**Aim #1**), the impact of low-frequency drug resistance mutations on response to ARV therapy (**Aim #2**), and the relative "transmission fitness" of mutant viruses (**Aim #3**). The project will be powered to perform the longitudinal analyses described in the first two studies with use of samples from *approximately 100* subjects who previously enrolled in the PIC Cohort study within 30 days after HIV-1 infection and from *80* subjects who will be enrolled prospectively. Eligibility will be restricted to subjects who acquired HIV-1 infection after 1996, when highly active ARV therapy became widely available in Seattle. OLA will be used to evaluate HIV-1 drug resistance in the PBMCs, blood and seminal plasma from ARV-naïve PIC subjects at baseline (the first available specimen), and 6 and 12 months after HIV infection (**Aim #1)** and in PBMCs 6 and 12 months after the start of ARV therapy (**Aim #2)** to detect changes in the levels of low-frequency HIV-1 drug resistance over time.

The third aim will study PIC subjects and their source partners enrolled in the PIC Cohort and PIC Partners studies. After the transmission relationships are confirmed by molecular methods, this cross-sectional analysis will compare the results of HIV-1 drug resistance testing performed on PBMCs and blood plasma from PIC subjects with the results of resistance testing performed on PBMCs, blood plasma, and genital secretions from their confirmed source partners. The partner-pairs studied in this third aim will also include retrospective analysis of previously collected specimens and continued prospective enrollment in order to maximize the precision of estimates of "transmission fitness" to be described in **5.c.3 Aim #3**.

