**Table 8: Estimated number of subjects with mutations in PBMCs and plasma over time**

| **8a**: Distribution of subjects at baseline | | | |
| --- | --- | --- | --- |
|  | | plasma | |
| - | + |
| PBMCs | - |  | *14 (41%)* |
| + | *8 (24%)* | *12 (35%)* |

| **8b**: Distribution of subjects at follow-up | | | |
| --- | --- | --- | --- |
|  | | plasma | |
| - | + |
| PBMCs | - | 12 (30%) | 4 (10%) |
| + | 18 (45%) | 6 (15%) |

| **8b**: Distribution of subjects at follow-up | | | |
| --- | --- | --- | --- |
|  | | plasma | |
| - | + |
| PBMCs | - | *20 (25%)* | *16 (20%)* |
| + | *40 (50%)* | *4 (5%)* |

+ = subjects w/ ≥1 mutation or mixture.

- = subjects w/o mutations or w/ indeterminate results

**Table 8**: The number of subjects who would have transmitted drug resistance identified in PBMCs and plasma at follow-up (**Table 8b and 8c**) was estimated for power calculations *based on the distribution of mutations identified at baseline (****Table 8a****) from the pilot project.*

Power calculations were performed using a two-sided McNemar's exact test with significance level of 0.05. We assumed that the baseline distribution of subjects with mutations in PBMCs, plasma, or both would be similar to that found in the pilot study *(****Table 8a):*** *25% in PBMCs, 40% in plasma, and 35% having mutations in both PBMCs and plasma).* In these power calculations, we estimated the proportion of these subjects who would have mutations detected in PBMCs and/or plasma *at the* follow-up *evaluation* (**Table 8b and *8c***). If *mutations initially detected in PBMCs and plasma remain detectable in 100% and 25% of subjects, respectively, in the follow-up specimen,* 30% of subjects who had transmitted HIV-1 drug resistance *will* no longer have detectable mutations, 10% of subjects *will* have mutations detected in plasma only, 45% of subjects *will* have mutations detected in PBMCs only, and 15% of subjects *will* continue to have mutations detected in both PBMCs and plasma (***Table 8b***). *With this distribution,* we would have 84% power to determine whether a significant difference exists in the detection of mutations in PBMCs versus plasma over time with 40 subjects who had transmitted HIV-1 drug resistance detected at baseline.

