*If the difference in loss of detection between PBMCs and plasma is less extreme, and 67% and 13% of mutations initially detected in PBMCs and plasma remain detectable in follow-up (****Table 8c****), then we would have 89% power to determine whether a significant difference exists in the detection of mutations in PBMCs versus plasma over time with 80 subjects who had transmitted HIV-1 drug resistance detected at baseline. Note that the McNemar's exact test takes account only of the distribution at follow-up and not changes over time; these calculations are therefore extremely conservative compared to the planned analysis described below.*

This sample size will be generated from previously enrolled subjects and from new enrollment. *There are 73 subjects among the entire PIC cohort who enrolled within 30 days of HIV-1 infection, who enrolled after 1996, and who have a median of 36 (range 0-139) months in follow-up.* Nine subjects studied through the pilot project were enrolled within 30 days of HIV-1 infection, had at least one low-frequency mutation identified, and have at least one year of follow-up in the cohort without ARV treatment. *Fifty-four subjects have enrolled in the cohort since the end of the pilot project, and we* anticipate that there will be an additional *15* subjects who will enroll before the start of this project, all of whom *will have been* enrolled within 30 days of HIV-1 infection. If we assume that *34*% of these subjects would have HIV-1 drug resistance mutations and *66% will remain ARV-naïve and in follow-up for at least one year*, we would expect that *15 previous-enrolled subjects will be eligible for study in Aim #1*. Prospective enrollment of *16* subjects with transmitted HIV-1 drug resistance in addition to the *24* previously-enrolled subjects would achieve the desired total sample size of 40. If *34*% of newly-enrolled subjects have transmitted HIV-1 drug resistance but *33*% of subjects initiate ARVs within 30 days after HIV-1 diagnosis, we would need to enroll *72* subjects by the end of the project period to achieve this sample size *(****Figure 5****).* Given our rate of enrollment in recent years, this number would be reasonably expected to accrue within the five years of the project.

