| Percent of subjects with no mutations at baseline who have new mutations detected after start of ARVs | 10% | *316/158* | *102/51* | *54/27* | *35/18* |
| 20% | *-* | *461/231* | *133/67* | *66/33* |
| 30% | *-* | *-* | *559/280* | *153/77* |
| 40% | *-* | *-* | *-* | *609/305* |

alpha = 0.05, power = 80%

The sample size for this aim will be motivated by a two-sample test of proportions that will compare the percentages of subjects with low-frequency mutations at baseline who have new mutations detected during ARV therapy compared to the percentage in subjects who had no mutations detected at baseline (**Table 9**). Estimates for the sample size calculations were informed by two small studies that identified increased numbers of HIV-1 drug resistance mutations in two (22%) of nine [32] and six (40%) of 15 [33] ARV-naïve subjects during ARV therapy. Based on these calculations and assuming that one-third of subjects will have transmitted drug resistance, a sample size of *53* treated subjects (*18 subjects with and 35 without drug resistance detected at baseline*) will have 80% power to detect a significant difference in the two groups if 50% of the subjects with baseline mutations and 10% of the subjects without baseline mutations have additional HIV-1 drug resistance mutations detected in PBMCs after the start of ARV therapy. There were 20 subjects who were studied as part of the pilot project who enrolled in the PIC Cohort study within 30 days of HIV infection, received ARV therapy for at least six months, and achieved virologic suppression. Another *twenty* subjects have enrolled in the PIC Cohort since the pilot study began and have received treatment *for at least six months*. If we estimate that *33*% of newly-enrolled subjects will initiate ARV therapy *in the first year of* follow-up *and assume a 10% loss-to-follow-up rate in the first year*, we would need to enroll *42* subjects in addition to these *40* subjects in order to achieve the desired sample size of *53* treated subjects (***Figure 5***)*.*

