**5.g Timetable for all projects**

Y1 0-6 months Submission of modification to IRB application

Confirmation of yet-to-be confirmed transmission pairs in PIC Partner Study

Continued enrollment in PIC Cohort and PIC Partners Studies (through Y5)

Y1-2 OLA of source and recipient partner-pairs (Aim #3)

Y2-3 OLA of untreated subjects (Aim #1)

Data analysis and manuscript preparation of Aim #3

Y3-4 OLA of treated subjects (Aim #2)

Data analysis and manuscript preparation of Aim #1

Y4-Y5 Data analysis, manuscript preparation of Aim #2 and future grant submission

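### Aim 1's route to 40 subjects counts all 54 post-pilot enrollees as enrolled within 30 days, which does not fit the cohort's own counts once pilot subjects are added, and the timetable tests specimens before the counted enrollees can supply them

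*Protocol*

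**What the plan says.** Protocol section 5.c.1 powers Aim 1 with a "two-sided McNemar's exact test with significance level of 0.05". With 45% of subjects positive in PBMCs only and 10% in plasma only (Table 8b), it claims 84% power at 40 subjects with baseline resistance.

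It reaches 40 as follows:
- Cohort total: "There are 73 subjects among the entire PIC cohort who enrolled within 30 days of HIV-1 infection, who enrolled after 1996".
- Pilot: nine subjects enrolled within 30 days, with a low-frequency mutation and at least a year of untreated follow-up.
- Since the pilot: "Fifty-four subjects have enrolled in the cohort since the end of the pilot project, and we" expects 15 more before the start. A within-30-days description closes that sentence. With 34% resistant and 66% still untreated and followed at one year, 15 are expected to be eligible.
- 9 + 15 = 24 previously enrolled. Another 16 are needed, from 72 new enrollees by the end of the project.

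Other sections bear on the same counts:
- Section 4.b: 78 subjects since 1992 "were enrolled within 30 days of their estimated dates of HIV-1 infection".
- Section 5.c.2: "There were 20 subjects who were studied as part of the pilot project who enrolled in the PIC Cohort study within 30 days" of infection, and these 20 were treated and suppressed.
- Section 4.g: 100 pilot subjects, with "plasma and PBMCs obtained a median of 29 (IQR 19-66) and 30 (IQR 19-66) days after HIV-1 infection".
- Section 5.a: about 100 "subjects who previously enrolled in the PIC Cohort study within 30 days after HIV-1 infection".
- Section 5.g: enrollment runs through year 5, but "Y2-3 OLA of untreated subjects (Aim #1") comes with Aim 1 analysis in years 3-4.

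**The concern.** The cohort total of 73 must hold both the pilot's within-30-day subjects and the post-pilot ones. If 54 of the 73 are post-pilot, 19 places remain for everyone earlier, and section 5.c.2 alone names 20. If 54 is too high, the 15, 24, 16 and 72 all change, and so does the assurance in the Introduction (Critique #1, item 4) that the primary objectives are adequately powered at the anticipated sample size.

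The timetable raises a second, independent problem. Aim 1 needs specimens 12 months after infection. The Introduction (Critique #3, item 3) says that fewer than five years is not feasible because all aims need the enrollment. Subjects who enroll late in the project cannot contribute to testing in years 2-3.

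**Working it through.** **1. The plan's own figures reproduce.**
- Supply: (54 + 15) × 0.34 × 0.66 = 15.5, stated as 15.
- 9 + 15 = 24, and 40 − 24 = 16.
- New enrollment: 16 / (0.34 × 0.66) = 71.3, stated as 72. With the 33% treatment-start figure, 16 / (0.34 × 0.67) = 70.2.
- Exact two-sided McNemar power at n = 40 with 0.45 and 0.10 is 84.4% (stated 84%). At n = 80 with 0.50 and 0.20 it is 88.9% (stated 89%).

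The within-30-days description could be read as covering only the 15 expected subjects. Those alone give 15 × 0.34 × 0.66 = 3.4, not 15, so the calculation uses all 54.

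**2. Does 54 fit?** Places left are 73 − 54 = 19 (after 1996) or 78 − 54 = 24 (since 1992).

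| Pilot subjects within 30 days | Basis | Plus 54 | Exceeds 73? | Exceeds 78? |
|---|---|---|---|---|
| 20 | section 5.c.2 | 74 | yes, by 1 | no |
| 29 | 20 + 9, if distinct | 83 | yes | yes |
| about 50 | half of 100, from the 29-30 day median | 104 | yes | yes |

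**3. Effect on n and power.** Let P be the pilot count and T the cohort total. The post-pilot ceiling is x = T − P, and the supply is e = (x + 15) × 0.34 × 0.66. With 72 enrolled, n = 9 + e + 16 (72 × 0.34 × 0.67 = 16.4; the plan uses 16). Enrollees needed for n = 40 are (31 − e) / (0.34 × 0.67). Power is taken at n rounded to the nearest whole subject.

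| P | T | x | e | 9 + e | n | Power | Enrollees for 40 |
|---|---|---|---|---|---|---|---|
| 20 | 73 | 53 | 15.3 | 24.3 | 40 | 84.4% | 69 |
| 29 | 78 | 49 | 14.4 | 23.4 | 39 | 83.4% | 73 |
| 29 | 73 | 44 | 13.2 | 22.2 | 38 | 82.4% | 78 |
| 50 | 78 | 28 | 9.65 | 18.65 | 35 | 78.9% | 94 |
| 50 | 73 | 23 | 8.5 | 17.5 | 34 | 77.5% | 99 |

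With P = 20 and T = 78 the ceiling is 58, so 54 fits.

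**4. Timetable, granting the stated 24.** Assume even accrual of 72 / 5 = 14.4 a year and specimens in hand by the end of year 3.
- 12-month specimen, so enrolled by the end of year 2: 28.8 × 0.34 × 0.67 = 6.6. Then 24 + 6.6 = 30.6, n of about 31, power 72.9%.
- At 57 / 3.5 = 16.3 a year (section 4.b, 2005 to mid-2008, any timing): 32.6 × 0.34 × 0.67 = 7.4, total 31.4, again about 31.
- Also counting subjects with only a 6-month specimen, so enrolled by mid-year 3: 36 × 0.34 × 0.67 = 8.2, total 32.2, n of about 32, power 74.6%.

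**5. Overview figure.** The 100 or so prior subjects in section 5.a compare with 73, or 73 + 15 = 88 with the expected enrollees.

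**The case against.** Much of the case on the other side stands.

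- A reader might infer that the totals 73 and 78 alone rule out 54. They do not, since 54 is below both. The conflict appears only when pilot subjects are added, and the strict excess is one subject over 73 and none over 78. Even that one could vanish: the pilot drew on enrollment from 1996 to 2005, while the 73 enrolled after 1996. If it is real, the supply becomes 15.3 and nothing downstream moves.
- The nine may overlap the 20. Section 4.g reports 28 subjects with low-frequency mutations, of whom 24 started treatment. On those counts at least five of the nine started later.
- The figure of about 50 is an inference. Blood is stored at screening, before entry, so specimen day is not exactly enrollment day. A reader might therefore take n of 34 and 78% power as established, but they are only the low end of a range.
- The 54 may be a sound count under the wrong label. Sections 3.a and 4.c define the population by Fiebig stages I to IV, and Table 2 lists about 132 such enrollees (1 + 13 + 74 + 6 + 1 + 37, including one pre-stage I). In that case the label needs correcting and n = 40 need not fall.
- Section 5.c.1 calls the McNemar calculation very conservative relative to the planned GEE analysis, which could also use 6-month data.
- A reader might divide a reduced post-pilot count by 3.5 years and project slow accrual and much lower power. No section gives the length of the post-pilot period, and ongoing eligibility requires screening within 30 days, so the documents do not support that projection.

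These points limit the size of the problem. They do not reconcile the counts, and they leave the schedule conflict in place.

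**Conclusion.** The point holds as an unreconciled input and an unreconciled schedule. The power formula is not in error.

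**Supply.** The yield of 15 requires all 54 post-pilot subjects to be within 30 days. That exceeds 73 for every pilot count considered, and exceeds 78 for the two larger ones. With 72 enrolled, n is about 34 to 40 and Table 8b power about 78% to 84%. Reaching 40 takes up to about 99 enrollees. The low end assumes that specimen day approximates enrollment day; the high end leaves the plan's figures unchanged.

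**Timetable.** As scheduled, n is about 31 to 32 and power about 73% to 75%, assuming even accrual and the stated 24. This does not depend on the pilot count. Any supply shortfall would add to it; the two are not combined here because the true pilot count is not stated.

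**What to change.** 1. Count post-pilot enrollees within 30 days from the cohort database. If another eligibility definition was meant, correct the 30-day label in section 5.c.1 and align it with sections 3.a, 4.c and 5.a.
2. Recompute 15, 24, 16 and 72 from that count, and restate expected n and power. No particular replacement figure should be written in before the recount.
3. Reconcile the figure of about 100 in section 5.a with 73 (88 with the expected 15).
4. In section 5.g, either schedule the last Aim 1 OLA batch and analysis late enough for the counted enrollees to reach 12 months, or count only those who will reach it in time and restate n and power.

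The cost is a database query, revised text and possibly a re-ordering of laboratory batches. The stated power may turn out less favorable.

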**5.c.2 Aim #2: Quantify the increase in detection of low-frequency mutations in PBMCs during ARV therapy.**

The primary objectives of the study described in this aim will evaluate changes in the detection of low-frequency mutations in PBMCs over time during ARV therapy and the virologic consequences of ARV therapy in the setting of transmitted low-frequency HIV-1 drug resistance. We hypothesize that, over time, additional mutations will be detected in a greater proportion of treated subjects with transmitted drug resistance compared to treated subjects without HIV-1 drug resistance detected at baseline, because the relative level to which viral replication is suppressed will be diminished in the former group. Secondary analyses will explore associations between specific HIV-1 drug resistance mutations, the interval between HIV-1 acquisition and the start of ARV therapy, the increased detection of HIV-1 drug resistance mutations, and treatment outcomes including time to virologic suppression and time to virologic failure.

This longitudinal study will evaluate subjects enrolled in the PIC cohort within 30 days of the estimated date of HIV-1 infection, who initiate ARV therapy at any point following the baseline evaluation, and who achieve undetectable HIV-1 RNA levels (less than 50 copies/mL) within six months after the start of ARV therapy. OLA will be performed using PBMCs collected at the visit immediately prior to the start of ARV therapy (unless this visit is within 4 weeks from the baseline specimen) and in specimens obtained 6 and 12 months following the start of treatment. The detection of a new mutation will be defined as any mutation detected during follow-up that was never previously detected. Additional analyses will use the semi-quantitative nature of OLA to evaluate the changes in levels of mutations during ARV treatment (i.e. <5%, 5-10%, 10-30%, 30-50% >50% of the viral quasi-species) and the reappearance of mutations that had been detected at baseline but were lost to detection prior to the start of ARV therapy in the absence of ARV selection pressures.

**Table 9: Sample size needed in each arm to detect a difference in proportion of subjects with new low-frequency mutations**

|  | | Percent of subjects with low-frequency mutations at baseline who have new mutations detected after start of ARVs | | | |
| --- | --- | --- | --- | --- | --- |
| 20% | 30% | 40% | 50% |
| Percent of subjects with no mutations at baseline who have new mutations detected after start of ARVs | 10% | *316/158* | *102/51* | *54/27* | *35/18* |
| 20% | *-* | *461/231* | *133/67* | *66/33* |
| 30% | *-* | *-* | *559/280* | *153/77* |
| 40% | *-* | *-* | *-* | *609/305* |

alpha = 0.05, power = 80%

The sample size for this aim will be motivated by a two-sample test of proportions that will compare the percentages of subjects with low-frequency mutations at baseline who have new mutations detected during ARV therapy compared to the percentage in subjects who had no mutations detected at baseline (**Table 9**). Estimates for the sample size calculations were informed by two small studies that identified increased numbers of HIV-1 drug resistance mutations in two (22%) of nine [32] and six (40%) of 15 [33] ARV-naïve subjects during ARV therapy. Based on these calculations and assuming that one-third of subjects will have transmitted drug resistance, a sample size of *53* treated subjects (*18 subjects with and 35 without drug resistance detected at baseline*) will have 80% power to detect a significant difference in the two groups if 50% of the subjects with baseline mutations and 10% of the subjects without baseline mutations have additional HIV-1 drug resistance mutations detected in PBMCs after the start of ARV therapy. There were 20 subjects who were studied as part of the pilot project who enrolled in the PIC Cohort study within 30 days of HIV infection, received ARV therapy for at least six months, and achieved virologic suppression. Another *twenty* subjects have enrolled in the PIC Cohort since the pilot study began and have received treatment *for at least six months*. If we estimate that *33*% of newly-enrolled subjects will initiate ARV therapy *in the first year of* follow-up *and assume a 10% loss-to-follow-up rate in the first year*, we would need to enroll *42* subjects in addition to these *40* subjects in order to achieve the desired sample size of *53* treated subjects (***Figure 5***)*.*

If no difference is identified between groups with and without transmitted HIV-1 drug resistance, an estimate of the proportion of all subjects with primary HIV-1 infection who have new HIV-1 drug resistance mutations detected in PBMCs during ARV therapy would be a novel finding of this study. **Table 10** shows the maximum 95% confidence intervals associated with varying sample sizes used to estimate the proportion of subjects who have new HIV-1 drug resistance mutations detected. If new HIV-1 drug mutations are not detected in any subjects during study follow-up, a sample size of 35 subjects would exclude the possibility that the true proportion of subjects with new mutations detected in PBMCs during virologic suppression is greater than 10%. If we identify significant numbers of subjects who have new HIV-1 drug mutations detected during follow-up, we will use logistic regression analyses to explore whether the detection of additional HIV-1 drug resistance mutations is associated with transmitted HIV-1 drug resistance, the timing of ARV therapy, the HIV-1 RNA level at the start of ARV therapy or rate of the initial viral decay, or treatment adherence.

